### 3.13. Statistical Analyses

All statistical analyses will be conducted using Statistica 13.1 PL (StatSoft Inc., Tulsa, OK, USA; StatSoft, Krakow, Poland). Categorical variables will be presented as a sample percentage (%). Continuous variables will be presented as means with 95% confidence intervals (95%CIs) for variables with a normal distribution or medians with an interquartile range (IQR) for variables with a non-normal distribution. To assess the impact of the nutritional intervention with probiotic supplementation and verify the differences between the experimental and control groups, multivariate analysis of variance and two-tailed tests will be applied. The normality of the variable distribution will be assessed using the Shapiro–Wilk test before statistical analysis. For continuous variables, e.g., diet quality scores, scores of quality of life, markers of adiposity, metabolic parameters, and changes after 12 weeks of education relative to baseline, will be assessed using a *t*-test for dependent samples for normally distributed variables or a Mann–Whitney test for variables without a normal distribution. Differences in categorical variables will be examined using the Pearson chi-squared test. *p* < 0.05 will be considered statistically significant.

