### 3.2. Selection of Participants

The selection of the sample for the study will be purposive, taking into account the inclusion and exclusion criteria. Recruitment for the study will be carried out using the snowball method, mainly via social networking sites (i.e., internet websites associated with Hashimoto’s patients). Additionally, collaboration with medical facilities and pharmacies will be established to reach a broader pool of potential participants. The CAWI (Computer-Assisted Web Interview) and PAPI (Paper and Pen Personal Interview) methods will be used for collecting data.

The inclusion criteria will be a medical diagnosis of Hashimoto’s disease based on anti-TPO, anti-TG, or an ultrasound image characteristic of AIDH; thyroid function status (euthyroid, hypothyroidism); female; age in the range of 18-64 years; normal body weight (body mass index BMI 18.50–24.99 kg/m^2^) or excessive body weight (BMI ≥ 25.00 kg/m^2^); and/or low-quality diet (low Pro-Healthy Diet Index (pHDI-10)) [36]. Women with contraindications to a body composition analysis performed using the electrical bioimpedance method (i.e., having a pacemaker) will also be included. However, for these patients, the body composition analysis stage will be skipped.

The exclusion criteria will be thyroid diseases other than AIDH, pregnancy, lactation, diagnosed cancer, and lack of consent to participate in the study. The individual must not take *Lp299v* or medications for weight loss or be diagnosed with celiac disease, Duhring’s disease, or a gluten allergy. The minimum number of subjects (47 for each group) was calculated based on an expected 50% improvement in the overall quality of life after 12 weeks of the intervention in the experimental group, with an assumed 5% significance level and 80% power. The baseline sample size of 100 patients was established to account for potential participant withdrawals.

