### 3.4. Course of Intervention

The 12-week intervention will involve individual nutrition education for patients with Hashimoto’s thyroiditis conducted in two groups. One group will additionally receive the *Lp299v* strain (NE + *Lp299v* group), and the other will receive a placebo (NE + P group). Before the start of education, an assessment of dietary habits will be performed using a three-day food record questionnaire. Additionally, validated tools will be used to assess (1) the dietary habits and nutritional beliefs (FFQ-6 and KomPAN^®^ questionnaire [36,37]); (2) the quality of life with thyroid diseases (ThyPROpl) [38]; (3) physical activity level (Polish version of IPAQ questionnaire) [39]. Anthropometric measurements (body weight and height, waist and hip circumferences), body composition, peripheral arterial pressure, and anti-TPO blood concentration measurements will also be performed. All parameters will be measured twice: at baseline and after 12 weeks of the intervention to evaluate changes and (if possible) compare the measurements to reference values. A diagram of the study is presented below (Figure 1).

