### 3.10. Anti-TPO Titer Concentration

The anti-TPO titer will be determined in venous blood taken from a peripheral vein of the forearm by qualified personnel from the medical laboratory. The concentration will be determined by immunochemistry on the “Alinity i” laboratory instrument and compared to a reference value of <5.61 IU/mL.

The factors influencing the anti-TPO result are anti-streptavidin and anti-ruthenium antibodies. Therefore, the measurement will be omitted for these patients. Biotin is also a factor that interferes with the anti-TPO titer measurement. Therefore, patients taking biotin supplementation will be advised to take a minimal break the day before the examination [52].

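### Section 3.13 fixes no baseline-adjusted arm comparison for the two primary outcomes, and its paired t-test/Mann–Whitney rule lets a normality test decide whether time points or arms are compared

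*Protocol article*

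**What the plan says.** The protocol article, section 2, makes the effect on body weight and on quality of life the primary objective. Section 3.4 states: "All parameters will be measured twice: at baseline and after 12 weeks of the intervention to evaluate changes". A baseline value is therefore planned for both primary outcomes.

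Section 3.13 sets out the analysis in three steps:

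- To assess the intervention and "verify the differences between the experimental and control groups", "multivariate analysis of variance and two-tailed tests will be applied". It does not say which outcomes enter, whether week-12 values or changes are analysed, or whether baseline or time is in the model. The two-tailed tests are not named.
- For continuous variables, "changes after 12 weeks of education relative to baseline" are to be assessed by a t-test "for dependent samples for normally distributed variables or a Mann–Whitney test for variables without a normal distribution". Normality is judged by Shapiro–Wilk.
- "Differences in categorical variables will be examined using the Pearson chi-squared test".

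The 95% confidence intervals in section 3.13 belong to the description of normally distributed variables. None is attached to a difference between arms.

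Two groups of women will lack some secondary measurements by design. Where bioimpedance is contraindicated, section 3.2 says that "for these patients, the body composition analysis stage will be skipped". Where interfering antibodies are present, section 3.10 says of the anti-TPO assay: "Therefore, the measurement will be omitted for these patients".

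**The concern.** The randomised contrast is Lp299v against placebo, on top of education that both arms receive (sections 3.4 and 3.11). The primary question therefore needs, for each primary outcome, an estimate of the difference between arms and its uncertainty. Section 3.13 does not clearly provide one.

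- An omnibus MANOVA p-value does not say whether weight or quality of life differed, or by how much.
- The one parametric univariate test named for continuous outcomes is paired. It measures everything that changed over 12 weeks in one arm: education, time, regression to the mean and, in one arm only, the probiotic.
- The alternative named for non-normal data is not the non-parametric counterpart of that test. It compares two independent groups, so the question changes with the shape of the data.
- Baseline values are collected, but no model is named that uses them as covariates.

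At stake are precision on the primary question and the risk that a significant change in one arm but not the other is read as a probiotic effect.

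**Working it through.** **1. The plan's own figure.** Section 3.2 gives 47 women per group for 5% significance and 80% power, from an expected 50% improvement in quality of life. It gives no standard deviation, control-arm value or responder rate, so 47 cannot be derived uniquely. Read as a two-sided comparison of two means, 47 per arm corresponds to a standardised difference of √(2/47) × (1.960 + 0.842) = 0.578 by the normal formula, or about 0.584 with the t distribution. These values are implied, not stated.

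**2. What the two tests compare.**

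| Shapiro–Wilk result | Test named | Comparison made |
|---|---|---|
| Normal | Dependent-samples t-test | Week 12 against baseline, within an arm |
| Not normal | Mann–Whitney | One independent group against another |

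The two rows answer different questions. The usual counterpart of the paired t-test is the Wilcoxon signed-rank test. The usual parametric counterpart of Mann–Whitney is the independent-samples t-test.

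**3. What separate within-arm tests would show.** Suppose that Lp299v adds nothing and both arms improve equally through education. Assumptions: 47 per arm, correlation 0.5 between baseline and week 12, common gain of 0.2, 0.3 or 0.4 SD. The SD of the change is √(2 × (1 − 0.5)) = 1, so the paired t-test has noncentrality gain × √47 and power p of about 0.27, 0.52 and 0.77. The chance that exactly one arm is significant is 2p(1 − p):

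- gain 0.2: 2 × 0.27 × 0.73 = 39%
- gain 0.3: 2 × 0.52 × 0.48 = 50%
- gain 0.4: 2 × 0.77 × 0.23 = 35% to 36%

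A simulation of 20,000 trials per setting gave 40%, 50% and 36%. A between-arm test of change was significant in about 5%, as it should be. Half of the discordant trials, 18% to 25% of all trials, would favour Lp299v.

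**4. What baseline adjustment is worth.** Assumptions: difference of 0.5 SD, 47 per arm, two-sided 5%, baseline correlation r of 0.5 to 0.7. Relative to the unadjusted week-12 value, the variance factor f is 1 − r² for ANCOVA and 2(1 − r) for change scores. Noncentrality is (0.5/√f) × √(47/2) = 2.424/√f. Power comes from the noncentral t with 92 degrees of freedom (91 for ANCOVA).

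| r | Week-12 value (f = 1) | Change score: f, power | ANCOVA: f, power |
|---|---|---|---|
| 0.5 | 67% | 1.00, 67% | 0.75, 79% |
| 0.6 | 67% | 0.80, 76% | 0.64, 85% |
| 0.7 | 67% | 0.60, 87% | 0.51, 92% |

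The difference 2(1 − r) − (1 − r²) equals (1 − r)², which is never negative. Apart from one degree of freedom, ANCOVA is therefore never less efficient than either alternative.

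**5. Comparison with MANOVA.** With 47 per arm, noncentrality is λ = (47/2) × μ′Σ⁻¹μ, and the test statistic follows F(p, 93 − p). Each shifted outcome is moved by 0.584 SD, at which a single unadjusted test has 80% power.

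- One shifted outcome among p uncorrelated ones: λ = 23.5 × 0.584² = 8.01, and power is 70%, 54% and 39% for p = 2, 5 and 10.
- Both of two outcomes shifted: λ = 2 × 8.01/(1 + r), where r is now the correlation between the two outcomes. Power is 95%, 88%, 83% and 78% at r = 0, 0.3, 0.5 and 0.7.

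MANOVA can thus lose or gain power, depending on the pattern of effects.

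**The case against.** The best defence is that the article condenses a fuller plan. Covariates and model form are commonly left to an analysis plan. The MANOVA could be run on changes or with time as a factor, and the word multivariate might loosely mean multi-factor. With randomisation, an unadjusted or change-score comparison remains valid, so ANCOVA is an efficiency gain and not a rescue. This stands as far as it goes: the lack of baseline adjustment is silence, and a reader who infers that the plan rules it out goes beyond the text.

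Three other stronger readings are also unsupported.

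- A reader might infer that every univariate test is within-arm. That is not so. Mann–Whitney compares independent groups, the chi-squared test is not limited to change within an arm, and the unnamed two-tailed tests belong to the sentence on comparing arms.
- A reader might infer that MANOVA costs power on the primary question. The loss in step 5 needs one shifted outcome among uncorrelated ones, whereas the second hypothesis in section 2 expects benefit on both quality of life and body weight.
- A reader might infer that women without bioimpedance or anti-TPO would drop out of the primary comparison. A complete-case MANOVA would do this only if those outcomes entered the same model as weight and quality of life. The article does not say so and gives no number of such women.

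Nor does the article say that efficacy will be claimed from discordant within-arm p-values. Step 3 shows a hazard, not a stated plan.

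The defence does not reach the test pair, which is written out in section 3.13 and is mismatched on its face. It also does not supply an arm-difference estimate for either primary outcome.

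**Conclusion.** The concern holds in a limited form. The text itself shows that the continuous-outcome rule pairs a within-arm test with a between-group test, so a normality check selects the question. It also shows that no arm difference with a confidence interval is promised for body weight or quality of life, and that no baseline covariate is named although baseline is measured.

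The power gain from ANCOVA over univariate unadjusted or change-score comparisons is general in direction. Its size is conditional: at an assumed 0.5 SD and 47 per arm, ANCOVA adds 12, 18 and 25 percentage points over week-12 values, and 12, 9 and 5 over change scores, at correlations of 0.5, 0.6 and 0.7. Neither the difference nor the correlation is given in the article. No general gain over MANOVA is established, and no loss of women from the primary analysis is shown.

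**What to change.** Rewrite section 3.13, before unblinding, along these lines:

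1. For each primary outcome, fit ANCOVA of the week-12 value on arm and the baseline value of that outcome, using all women who have that outcome.
2. Base conclusions on the adjusted Lp299v-minus-placebo difference with its 95% confidence interval.
3. Label within-arm tests descriptive, and use a matching pair for them: paired t-test with Wilcoxon signed-rank.
4. If MANOVA is kept, make it supportive and list the outcomes that enter it.

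The cost is wording. The baseline data are already planned, standard software fits the model, and no visit, measurement or participant is added.

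If a fuller analysis plan already specifies such a model, it is enough to align section 3.13 with it and correct the test pair.

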## 2. Study Aim and Hypothesis

The primary objective of the trial is to assess the effect of a dietary intervention with probiotic *Lp299v* supplementation on body weight and quality of life in female AIDH patients.

The secondary objective of the trial is to evaluate the effectiveness of individual personalized nutritional counseling on several key parameters among patients diagnosed with Hashimoto’s thyroiditis. The specific focus areas for assessment include food selection and diet quality, body composition, serum anti-TPO, and blood pressure.

The research hypotheses are as follows:-Individual personalized nutrition education aimed at improving food selection and diet quality may enhance nutritional status, anti-TPO parameters in the blood, and the overall quality of life in AIDH patients.-The *Lp299v* strain may augment the impact of the individual nutritional intervention, particularly in terms of improving the quality of life, body weight status, and anti-TPO parameters in the blood.

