### 3.7. Quality of Life

The quality of life of the participants will be assessed using the Quality of Life Questionnaire for Patients with Thyroid Diseases (ThyPROpl).

ThyPROpl is a thyroid-specific questionnaire validated for the Polish population by Sawicka-Gutaj et al. [38]. The questionnaire comprises 85 questions grouped into 13 scales measuring aspects of quality of life relevant to thyroid patients. The 13-point scale includes questions on (1) symptoms, (2) feeling tired, (3) energy, (4) memory and concentration, (5) nervousness and tension, (6) mental well-being, (7) problems with coping or mood swings, (8) relationships with other people, (9) daily activities, (10) sex life, (11) the impact of the disease or its treatment on appearance, (12) the intensity of the impact of the disease on the subject in general. All quality-of-life questions will cover the last 4 weeks prior to the survey. The respondents must choose 1 of 5 answer categories: (1) not at all, (2) a little, (3) average, (4) quite a lot, (5) very much. In the question regarding difficulties in performing duties at work, the authors added an additional category—“I do not work” [38]. The score ranges from 0 to 100, with higher scores indicating a poorer quality of life.

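### A Shapiro–Wilk pretest decides whether an outcome, primary ones included, gets a within-arm t-test or a between-arm rank test, so the sample settles what is estimated

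*Protocol article*

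**What the plan says.** All of the following is in the protocol article.

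- **Pretest (3.13).** "The normality of the variable distribution will be assessed using the Shapiro–Wilk test before statistical analysis". No significance level is given for it.
- **Summary (3.13).** Continuous variables are shown as "means with 95% confidence intervals (95%CIs) for variables with a normal distribution or medians with an interquartile range (IQR") for those that are not normal.
- **Test (3.13).** A t-test for "dependent samples for normally distributed variables or a Mann–Whitney test for variables without a normal distribution".
- **Variables covered (3.13).** The list is illustrative and includes "scores of quality of life, markers of adiposity, metabolic parameters, and changes after 12 weeks of education relative to baseline". Body weight is not listed by name, but adiposity markers are, and no continuous variable is exempted.
- **Group comparison (3.13).** For the intervention's effect and the differences between groups, "multivariate analysis of variance and two-tailed tests will be applied". No effect measure is attached.
- **Primary objective (section 2).** The effect of the dietary intervention with the probiotic "on body weight and quality of life in female AIDH patients".
- **Quality-of-life scale (3.7).** "The score ranges from 0 to 100, with higher scores indicating a poorer quality of life".

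**The concern.** A plan should fix, before the data are seen, what quantity the primary analysis estimates. Here a test on the data does that. A mean and a rank comparison already target different quantities. In this text the branches also differ in a more basic way: a dependent-samples t-test asks whether women changed from baseline within an arm, whereas Mann–Whitney compares two independent groups.

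Both arms receive the same nutrition education, so improvement in both is what the investigators expect. A within-arm test will detect that improvement whether or not the probiotic adds anything. If the pretest sends the primary outcome down the normal branch, a significant result can be read as a probiotic effect when it shows only the shared education effect.

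Neither branch names an estimate of the arm difference with a confidence interval. The interval in the normal branch is for a mean, and the IQR in the other branch describes spread between patients. Neither tells the reader what size of probiotic effect a null result would exclude.

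**Working it through.** **Inputs.** Arm size 47 (section 3.2, minimum per group). Two-tailed testing at 0.05 (3.13). Assumed, because the documents do not give them: a 5% level for the pretest, the shape of the outcome distributions, and the size of the shared improvement in units of the SD of the change.

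**The plan's own figure.** The 47 per group cannot be rebuilt from the stated 50% improvement, because no SD or control value is given. It corresponds to a standardised difference of (1.960 + 0.842) × √(2/47) = 0.578 at 80% power, two-sided. The total of 100 allows for 1 − 94/100 = 6% withdrawals. The 47 is used below only as the arm size.

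**Step 1: if both branches compared the arms.** Simulation, 5,000 trials per setting, pretest on pooled arm-centred changes, then independent t-test or Mann–Whitney.

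| Distribution of change | Pretest rejects (no effect) | Type I error: t | Type I error: gated | t and rank disagree at 0.578 |
|---|---|---|---|---|
| Normal | 5.5% | 4.8% | 4.9% | 5.7% |
| Gamma, shape 10 | 55.9% | 5.2% | 5.5% | 6.6% |
| Gamma, shape 4 | 92.6% | 5.2% | 4.6% | 7.7% |
| Lognormal, sigma 0.5 | 99.6% | 4.3% | 4.5% | 13.4% |

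Type I error stays near 5% throughout. The plain t-test holds it too, so the pretest is not needed to protect a mean comparison at this size.

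**Step 2: the branches as written.** Both arms improve equally by 0.5 SD and the probiotic has no effect. For normal changes, the paired test in one arm has non-centrality 0.5 × √47 = 3.43. Against a critical t of 2.013 on 46 df, the chance of significance is 91.9%. By simulation:

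| Distribution of change | Paired t, experimental arm | Mann–Whitney between arms | Result after the pretest |
|---|---|---|---|
| Normal | 92.0% | 5.0% | 88.0% |
| Gamma, shape 10 | 94.4% | 5.0% | 44.7% |
| Gamma, shape 4 | 95.5% | 4.3% | 10.2% |
| Lognormal, sigma 0.5 | 97.0% | 4.9% | 5.2% |

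With a shared improvement of 0.3 SD, the paired test is significant in 52 to 53% of trials and Mann–Whitney in about 5%. The last column shows the problem: with no probiotic effect, the chance of a significant result runs from about 5% to 88%, depending on which question the pretest selects.

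**Step 3: how often the pretest fires.** This depends on distributions that the documents do not give.

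- *Raw 0–100 scores, beta, mean 25–45, SD 15–20.* At n = 94, rejection runs from about 6–7% (mean 45, SD 15) to 100% (mean 25, SD 20). At n = 47 it runs from about 5% to 96%.
- *Raw body weight, lognormal, CV 0.15–0.22.* About 33–59% at n = 94 and 20–33% at n = 47.
- *Changes, assumed pre/post correlation 0.5–0.7.* About 4–24% for score changes from means of 35–45, 27–89% from a mean of 25 with a large improvement, and 4–19% for weight changes.

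**The case against.** **MANOVA is the between-group analysis, and it is not gated.** It is named for group differences, in a sentence before the pretest. But it stands beside unspecified two-tailed tests, carries no effect measure, and is not said to be primary or to override the gated tests. This means one cannot say the gated test is certainly the primary result. It does not settle which result is.

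**The paired/unpaired pairing may be a slip.** Perhaps a signed-rank test was meant, or an independent t-test. If the former, both branches are within-arm and neither compares the groups. If the latter, Step 1 applies and the error rate is sound, but the sample still chooses between a mean and a rank comparison. Either way the text needs correcting.

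**Normality may be tested on changes, not only raw values.** Section 3.13 does list 12-week changes. This objection stands: a reader should not infer that only raw variables are tested.

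**The mean/median sentence is descriptive, and a condensed article may leave effect estimates to the full plan.** Also fair. Silence alone would be no finding. The finding is the positive rule the article states, which lets the pretest select the test and the summary.

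**Conclusion.** The point holds as a flaw in the stated rule. The pretest settles what is estimated for outcomes that include the primary ones, and its branches answer different questions. The size is the gap in Step 2: about 92–97% against about 5% significant when both arms improve by an assumed 0.5 SD and the probiotic does nothing. It rests on 47 per arm, a 5% pretest and the assumed distributions.

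Four stronger readings are not supported:

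- A reader might infer that choosing between t and rank inflates type I error. It stays at 4.5–5.5%.
- A reader might infer that the route is close to a coin toss for both primary outcomes. That fits some assumed distributions only; the rate runs from about 6% to 100% for raw scores and is lower in most settings for changes.
- A reader might infer that the two arms could get opposite verdicts. Section 3.13 does not say that normality is tested arm by arm.
- A reader might infer that only non-normal outcomes lack an effect estimate. Neither branch names an arm difference with an interval.

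**What to change.** Delete the Shapiro–Wilk gate from section 3.13. For ThyPROpl and for body weight, pre-specify one between-arm linear model of the 12-week value or the change, adjusted for the baseline value that is already collected. Report the arm difference with its 95% CI whatever the distribution looks like. Check residuals graphically, and keep rank or bootstrap results as sensitivity analyses only. State how MANOVA relates to these models, or remove it. Label within-arm changes as descriptive and not as evidence of a probiotic effect.

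The cost is analysis wording only. No new data, visits or participants are needed.

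### Section 3.13 offers a paired t-test and the Mann–Whitney test as alternatives for the same baseline-to-week-12 comparison; one of the two is wrong on either reading

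*Protocol article*

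**What the plan says.** Section 3.4 (Course of Intervention) sets up paired data: "All parameters will be measured twice: at baseline and after 12 weeks of the intervention to evaluate changes".

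Section 3.13 (Statistical Analyses) makes four statements that bear on the point:

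- Between arms: to "verify the differences between the experimental and control groups, multivariate analysis of variance and two-tailed tests will be applied". No univariate test is named here.
- Choice of test: "The normality of the variable distribution will be assessed using the Shapiro–Wilk test before statistical analysis".
- Continuous outcomes: diet-quality scores, quality-of-life scores, "markers of adiposity, metabolic parameters, and changes after 12 weeks of education relative to baseline, will be assessed" with a t-test "for dependent samples for normally distributed variables or a Mann–Whitney test for variables without a normal distribution".
- Categorical outcomes: "Differences in categorical variables will be examined using the Pearson chi-squared test". It does not say whether these differences are between arms or between visits.

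No paired rank test is named anywhere in the article.

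**The concern.** One sentence gives two tests as interchangeable options for one comparison, depending only on the shape of the distribution. They do not answer the same question. The dependent-samples t-test uses each woman as her own control. Mann–Whitney compares two unrelated groups and has no place for pairing. Its non-parametric counterpart for paired data is the Wilcoxon signed-rank test.

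The within-woman analyses matter in this trial. Both arms receive the nutrition education, so the secondary objective and the first hypothesis in section 2 (the effect of counselling itself) can only be examined through change from baseline. The sentence also covers quality of life, which is part of the primary objective. Any outcome that fails Shapiro–Wilk is sent to the unpaired test. A skewed antibody titre is an obvious candidate and bounded questionnaire scores are plausible ones, although the article gives no distributions, so this is an expectation.

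**Working it through.** **Step 1. Which comparison does the sentence describe?**

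| Reading | t-test for dependent samples | Mann–Whitney |
|---|---|---|
| Change within the same women, week 12 against baseline | correct | wrong: the samples are not independent |
| Change scores compared between NE + *Lp299v* and NE + P | wrong: women in the two arms are not paired | correct |
| t-test meant within arms, Mann–Whitney meant between arms | no rank test for within-arm change | no parametric counterpart between arms |

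No reading gives a complete, valid pair of tests. The first is the natural one, because the sentence speaks of change relative to baseline and the between-arm question has its own earlier sentence.

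**Step 2. Inputs for the size of the error.** From the documents: 47 women per group as the minimum (section 3.2) and two-sided testing at 5% (section 3.13). Assumed, because the article gives no values: the pre–post correlation (range 0 to 0.9), a log-normal outcome with log-scale SD 0.8, and shifts of 0.3 or 0.4 log-scale SD. These shifts lower the median by 1 − exp(−0.3 × 0.8) = 21% and 1 − exp(−0.4 × 0.8) = 27%.

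The plan gives no figure on this point to reproduce. The 47 per group serves only as a sample size here. It cannot be rebuilt, since section 3.2 states neither a control value nor an SD.

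**Step 3. Approximate type I error by formula.** Mann–Whitney takes the variance of the rank difference as if the visits were independent. With rank correlation ρₛ the true variance is smaller by the factor (1 − ρₛ), so the actual error is about 2·Φ(−1.96 / √(1 − ρₛ)). For a normal or log-normal pair with correlation ρ on the log scale, ρₛ = (6/π)·arcsin(ρ/2).

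- ρ = 0.3: ρₛ = 0.288; 1.96/√0.712 = 2.32; error about 2.0%
- ρ = 0.5: ρₛ = 0.483; 1.96/√0.517 = 2.73; error about 0.6%
- ρ = 0.7: ρₛ = 0.683; 1.96/√0.317 = 3.48; error about 0.05%

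**Step 4. Simulation, 47 pairs, two-sided 5%** (10,000 replicates; 4,000 for the 0.4 SD column). Each cell shows Mann–Whitney / Wilcoxon signed-rank.

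| ρ | Type I error | Power, 0.3 SD | Power, 0.4 SD |
|---|---|---|---|
| 0 | 5.0% / 5.1% | 29% / 27% | – |
| 0.3 | 2.1% / 4.8% | 26% / 35% | – |
| 0.5 | 0.8% / 5.0% | 22% / 45% | 46% / 70% |
| 0.7 | 0.04% / 4.8% | 18% / 65% | 45% / 88% |
| 0.8 | 0.01% / 4.6% | 14% / 83% | 45% / 97% |
| 0.9 | 0% / 5.0% | 9% / 98% | – |

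The simulated errors agree with the formula. Repeat runs at ρ from 0.5 to 0.8 gave power figures within about two percentage points. With both arms pooled (94 women, 0.3 SD), power is 52% against 75% at ρ = 0.5 and 52% against 92% at ρ = 0.7.

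**Step 5. Direction.** For any positive correlation the Mann–Whitney p-values are too large. They are right only at zero correlation, which is not credible for weight, waist circumference or an antibody titre measured twice in the same woman.

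**The case against.** The strongest counter-argument concerns reach. The randomised *Lp299v* comparison has its own sentence in section 3.13, so on the within-woman reading the faulty sentence does not test the effect that randomisation and blinding protect. The within-woman changes have no uneducated control group, so even a correct paired test could not show that education caused them. The error is also conservative and produces no false positives. This all stands, and it limits the consequence to missed changes in the pre–post analyses. It does not repair the sentence: the between-arm statement names only multivariate analysis of variance and unspecified two-tailed tests, so it supplies no valid univariate pair.

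A second argument is that the sentence is grammatically broken and may have meant between-arm comparison of changes, where Mann–Whitney is sound. That is possible, but the dependent-samples t-test is then the wrong partner. The fault moves to the other branch.

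A third is that the chi-squared rule is not shown to be wrong. That is fair: Pearson's test is correct between arms and would be wrong only if applied to paired categories, such as BMI class before and after. The article does not say which is meant, so this part of the point is conditional.

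**Conclusion.** The point holds. As written, section 3.13 assigns a paired and an unpaired test to the same comparison, and one of them is wrong whichever comparison was intended. If the sentence is followed for within-woman change, non-normal outcomes get p-values that are too large: at assumed correlations of 0.5 to 0.8 the actual error rate is below 1%, and power for a 0.3 SD shift falls from 45–83% to 22–14%. These sizes rest on the assumed correlation, shift and log-normal shape. The direction needs only a positive within-woman correlation. The between-arm comparison is not invalidated by this fault. It should be corrected before analysis: otherwise the investigators must either report an invalid test or depart from the published plan once data are in hand.

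**What to change.** Rewrite the sentence in section 3.13 so that each test is tied to one comparison:

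- Within-woman change, baseline to week 12: dependent-samples t-test, or the Wilcoxon signed-rank test if the differences are not normal. Apply the normality check to the differences, not to the raw values at each visit.
- Between NE + *Lp299v* and NE + P: independent-samples t-test or Mann–Whitney test on the change scores, alongside the multivariate analysis already planned.
- Categories: Pearson chi-squared between arms. If before–after categories are to be tested, McNemar's test for two classes.

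This costs a sentence or two of text. It needs no further data, visits or participants.
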